#### **4.4.7 Four Step Square Test (FSST)**

The Four Step Square Test (FSST) (Dite and Temple, 2002) addresses balance and the ability to step forward, sideways and backward over obstacles.

##### **4.4.7.1 Implementation**

The test persons stand in a square, which is formed by a wooden cross lying on the floor. The test persons are asked to step clockwise and then counterclockwise into all four squares. To do this, they must step forwards, sideways and backwards over the cross lying on the floor. There are always two runs, a trial run and a run in which the time is stopped. The execution time is less than 5 minutes.

#### **4.4.8 10-metre walk test**

##### **4.4.8.1 Implementation**

This test of walking speed is an important secondary outcome parameter. It is highly recommended by the Parkinson's Taskforce (PD EDGE) for patients with IPD in a H & Y stage 1-3. Crossing a road with or without traffic lights requires the ability to travel a short distance at the highest possible speed. If this ability is not sufficiently present, activities in the area of participation are significantly limited. In this test, lines are placed on the ground marking the start, 2m, 8m and 10m. The time between the 2m and 8m line is measured to exclude the acceleration and deceleration phases. The time taken to cover these 6m is written down to the hundredth of a second. The 6m is then divided by the time taken (in seconds). This gives the speed in m/s. Two runs are made in this way and the average is used. Aids that the patient is currently using may be used. Any aid used must be documented. When the examiner is giving the test instructions, it must be ensured that the examiner is not in front of or directly next to

the patient and that he/she does not interfere with the patient's performance of the test. The examiner should be at least half a metre behind the patient.

#### **4.4.8.2 Psychometric criteria**

The Standard Error of Measurement (SEM) is reported to be 0.04 m/s and the Minimal Clinically Important Difference (MCID) is reported to be 0.18 m/s at comfortable walking speed and 0.25 m/s at maximum speed. (Steffen and Seney, 2008). The test-retest reliability of the 10MWT is excellent in individuals with PD (ICC = 0.96- 0.97). (Steffen and Seney, 2008) as is the inter-rater reliability (ICC=0.93-0.99). (Lindholm et al., 2018). A low standard error of measurement of 0.032-0.076 m/s and high predictive validity were shown with an Area under the Receiver Operating Characteristic Curve (ROC) of 0.70-0.73 with respect to the risk of falling (Lindholm et al., 2018). Cut-off values for IPD patients were 1.1-1.2 m/s (Lindholm et al., 2018).

#### **4.4.8.3 Psychometric criteria**

Duncan and Earhart (2013) evaluated a cut-off value for a high risk of falling at >9.68 seconds for people with idiopathic Parkinson's syndrome. The inter-rater reliability is very high with an ICC value of 0.99. For criterion validity describe Duncan and Earhart (2013) show a strong correlation of the FSST compared with the UPDRS Scale III ( $r = 0.61$ ) and a moderate correlation with the FOG-Q ( $r = 0.44$ ).

#### **4.4.9 Parkinson's Disease Questionnaire (PDQ-39)**

The PDQ-39 (Berger et al., 1999; Peto et al., 1995) is used to assess health-related quality of life and is a secondary endpoint of this study. Written permission to use the German version of the PDQ-39 in this study was obtained from Mapi Research Trust.

##### **4.4.9.1 Implementation and evaluation**

The PDQ-39 is a 39-item questionnaire for self-evaluation of health-related quality of life (Patient Rated Outcome Measure, PROM). It consists of 8 dimensions: Mobility (items 1 to 10, max. 40 points), daily activities (items 11 to 16, max. 24 points), emotional well-being (items 17 to 22, max. 24 points), stigma (items 23 to 26, max. 16 points), social support (items 27 to 29, max. 12 points), cognition (items 30 to 33, max. 16 points), communication (items 34 to 36, max. 12 points), physical discomfort (items 37 to 39, max. 12 points). The evaluation is based on a 5-point Likert scale, from 0 = "Never" to 4 = "Always". Recoding of the response categories is not necessary for the creation of the subscales. All 8 domain scores and the Global Index are standardised on a 0-100 scale, with 0 representing the best health-related

QoL and 100 the worst. Mapi Trust provides an SPSS syntax for scoring. The index can only be calculated in each case if the percentage of missing data for all dimensions is  $\geq 50\%$ . The PDQ-39 takes 10-20 min to complete.

The evaluation is based on the evaluation instructions for the German version of the PDQ-39 (Berger et al., 1999).

### Subscales

The 39 individual items of the PDQ-39 are added to the following 8 subscales: Mobility, Activities of Daily Living, Emotional Well-being, Stigma, Social Support, Cognition, Communication, Physical Discomfort. The assignment of the corresponding items to the 8 subscales are shown in table 3.

**Table 3:** PDQ-39 subscales and assigned items

|                                                                                                                                                                                                                            |                                                                                                                 |
|----------------------------------------------------------------------------------------------------------------------------------------------------------------------------------------------------------------------------|-----------------------------------------------------------------------------------------------------------------|
| Mobility (10 items)
Leisure activities
Household activities
Shopping
Walk 1 km
Walk 100 m
Move around the house
Move around in public
Escort needed
Fear of falling
Tied to the house | Stigma (4 items)
Hide illness
Avoid situations
Shame
Worries about reactions                 |
|                                                                                                                                                                                                                            | Social support (3 items)
Problems with people
Support spouse
Support friends                    |
| Everyday activities (6 items)
Washing problems
Tightening problems
Buttoning problems
Indistinct writing
Cut food into small pieces
Spill a drink                                                 | Cognition (4 items)
Fall asleep during the day
Concentration problems
Poor memory
Bad dreams |
|                                                                                                                                                                                                                            | Communication (3 items)
Speech difficulties
Communication problems
Lack of attention            |
| Emotional well-being (6 items)
Feeling depressed
Loneliness
Near tears
Being angry
Be anxious                                                                                                        | Physical discomfort (3 items)
Muscle cramps
Joint pain
Feeling hot/cold                         |

|                          |  |
|--------------------------|--|
| Worries about the future |  |
|--------------------------|--|

The 5 answer categories are coded as follows: 0 = never, 1 = rarely, 2 = sometimes, 3 = often, 4 = always or I cannot do it at all. Recoding of the answer categories is not necessary for the creation of the subscales.

For each subscale, a raw score is first calculated by adding the associated individual items for each patient. By transforming the raw scores to a scale between 0 (=best) and 100 (=worst), the individual scale scores become comparable. The following formula is used for the transformation:

$$\frac{(\text{raw scale value} \times 100)}{\text{maximum scale value}}$$

(examples: Raw scale value of a patient for 'Mobility' = 30  $\Rightarrow$  30 x 100 / (4 x 10) = **75**)

Raw scale value for 'Stigma' = 4  $\Rightarrow$  4 x 100 / (4 x 4) = **25**)

The values obtained by transformation correspond to a patient's PDQ scores on the corresponding subscale. In our example, a score of 75 on the 'Mobility' subscale means that the patient has achieved a score that is 75 per cent worse than the best possible score. Similarly, a score of 25 on the 'Stigma' scale means that this patient has achieved a score that is 25 per cent below the best achievable score.

### Missings

The handling of missing answers (missings) requires special attention. Since they cannot be avoided in self-answering, the following procedure is recommended. If at least 50 per cent of the items of a subscale have been answered, the missing answers are replaced by the mean value of the existing answers in this scale. This means that in the 10 item scale a maximum of 5 questions may remain without an answer, in the 6 item scales a maximum of 3, in the 4 item scales a maximum of 2 and in the 3 item scales only one question. After replacing the missing answers with the mean values of the existing ones within a subscale, the sum scores of the eight subscales are calculated by addition and transformation as described above. When collecting the PDQ answers in the interview, no missings should occur.

### PDQ - 39 Total Score (PDSI)

A PDQ-39 sum score (PDQ-39 SI) can be calculated from the 8 subscales. It represents the mean value of the 8 subscales, weighted by the number of items. For its calculation, the

PDQ values of each scale are added up for each patient and the sum divided by 8 (=number of scales).

$$[\text{Mobility} + \text{Activities of daily living} + \text{Emotional well-being} + \dots + \text{Physical Discomfort}] / 8 = \text{PDQ-39SI}$$

When interpreting the PDQ-39 SI, its weighting by the number of corresponding questions per scale must be taken into account. As a composite score, it is generally less sensitive to change than the subscales of primary interest.

#### **4.4.9.2 Psychometric criteria**

All seven of the eight dimensions of the PDQ-39 showed satisfactory discriminant validity (Schrage, 2000). Internal consistency is excellent (Cronbach's alpha = 0.84-0.94). (Jenkinson et al., 1997).. The Standard Error of Measurement (SEM) is reported by XXX for the 8 dimensions as follows: Mobility (5.85-11.61), Activities of daily living (6.96-11.46), Emotional well-being (8.26-13.56), Stigma (5.57-13.67), Social support (7.84-17.61), Cognition (8.54-12.34), Communication (6.67-14.95), Physical discomfort (9.94-16.37). (Martinez-Martin et al., 2007). Excellent convergent validity was found with moderate to strong significant correlations of the PDQ-39 with Hoehn & Yahr stage ( $r = 0.60$ ), UPDRS-ME ( $r = 0.41$ ) and SF-36 ( $r = 0.34-0.80$ ). (Schrage, 2000). Satisfactory internal and external validity as well as acceptable reliability were found for all eight dimensions of the PDQ-39 (Jenkinson et al., 1997).. According to Jenkinson and colleagues (1997), the PDQ-39 better represents the impact of QoL in people with Parkinson's disease than generic measures such as the Short Form-36 Health Survey (SF-36).

#### **4.4.10 Freezing of Gait Questionnaire (FOG-Q)**

The Freezing of Gait Questionnaire (Giladi et al., 2000) is a valid instrument for assessing FOG in people with idiopathic Parkinson's syndrome without dementia. The FOG-Q was validated for German-speaking countries in 2015. (Vogler et al., 2015). It is used to quantify the FOG. Due to its short implementation time and high practicability, the FOG-Q is very well suited for assessing FOG in clinical practice.

##### **4.4.10.1 Implementation**

The FOG-Q is a PROM for the evaluation of FOG. It contains 6 items, which are collected from the persons with Idiopathic Parkinson's Syndrome or, if necessary, as an interview from the responsible doctors or therapists. The evaluation is based on a 4-point Likert scale, from 0=

"normal" to 4= "unable to walk", with higher scores representing more pronounced freezing. The questions address whether FOG is present, whether daily life is affected by it and whether freezing occurs when walking or turning. The procedure requires 5-10 min.

#### **4.4.10.2 Psychometric criteria**

The construct validity of the German version of the FOG-Q was tested in 27 persons with Idiopathic Parkinson's Syndrome (Hoehn & Yahr II-IV) with FOG. The FOG-Q has good internal consistency (Cronbach's  $\alpha$ : 0.83). A significant correlation was demonstrated between the Freezing item (2.13) and the MDS-UPDRS ( $p=0.002$ ) and mobility or activities of daily living of the PDQ-39 ( $p=0.006$  and  $p= 0.035$ , respectively). The results showed no association between the FOG-Q and the MDS-UPDRS subscale I ( $p= 0.079$ ), indicating good divergent validity. (Vogler et al., 2015).

#### **4.4.11 Falls Efficacy Scale- International Version (FES-I)**

A large number of older people have psychological problems that are related to falls. This applies both to people who have already fallen and to people who have not yet fallen. In order to address these problems, it is necessary to assess fear of falling and self-efficacy in relation to falling. The Falls Efficacy Scale (Tinetti et al., 1990) was extended to an international version (FES-I) in 2005 by an expert network on fall prevention (Prevention of Falls Network Europe, ProFaNE). (Yardley et al., 2005; Skelton et al., 2004). The PROM is used to assess fall-associated self-efficacy in older people. With the extension, more complex, functional activities and social aspects of self-efficacy were included.

##### **4.4.11.1 Implementation**

The FES-I consists of 16 items that evaluate the concerns about falls and various activities in the subjects. The questionnaire can be administered as a self-report questionnaire or as a structured interview. The answers are ranked on a 4-point Likert scale from 1= "no concerns" to 4= "very great concerns". The duration of the questionnaire is 10 minutes.

##### **4.4.11.2 Psychometric criteria**

In the course of the further development of the FES into the FES-I by the expert network on fall prevention (Prevention of Falls Network Europe ProFaNE), a German translation was made. However, validation is only available for the English version. (Skelton et al., 2004). The results of the English version show a high retest reliability for the total score ( $r= 0.96$ ) and a

high internal consistency (Cronbach's  $\alpha = 0.96$ ). Furthermore, the item intercorrelation was on average  $r = 0.55$  (range  $r = 0.29-0.79$ ). (Dias et al., 2006).

#### **4.4.12 Beck Depression Inventory (BDI-II)**

The BDI-II (Beck et al., 1988) is used to assess the severity of depression and is a secondary endpoint of this study. Written permission to use the German version of the BBD-II in this study was obtained from the Mapi Research Trust (fee required; <https://mapi-trust.org/>).

##### **4.4.12.1 Implementation**

The BDI-II consists of 21 items and is a PROM for assessing the severity of depression. The items are evaluated on a 4-point Likert scale from 0 to 3, which means that the sum of the items can be 0-63 points. A depression can be identified if the score is greater than 10. The scale is validated from the age of 13. The duration of the questionnaire is 5-10 minutes.

##### **4.4.12.2 Psychometric criteria**

The internal consistency is excellent (Cronbach's  $\alpha = 0.89-0.93$ ). The reliability for a sample of depressed test persons is 0.92. The reliability for healthy persons is 0.80 and 0.82. The retest reliability for healthy persons can be regarded as sufficiently stable, as it is 0.78 over three weeks and five months. The retest reliability is lower for test persons with a value of 0.46. The criterion validity in relation to the correlation with quality of life shows values between 0.50 and 0.75. (Kühner et al., 2007).

For subjects with idiopathic Parkinson's syndrome, a test-retest stability with an ICC value of 0.89 could be determined. (Visser et al., 2006). For persons with psychiatric disorders, the following cut-off values could be determined: Minimal depression is identified from a score of 10.9 (SD=8.1) points, mild depression from a score of 18.7 (SD=10.2) points, moderate depression from a score of 25.4 (SD=9.6) points, severe depression is present from a score of 30.00 (SD=10.4) points. (Beck et al., 1988).

#### **4.4.13 Fall rate**

There is a survey of the number of falls

- (a) in the 3-month period before the start of the study (subjectively asked at baseline)
- (b) in the 4-week intervention period (observed and subjectively asked about post-intervention)
- (c) in the 4-week follow-up period (subjectively asked during the follow-up call)

The number of falls is documented in the CRF.

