### 4.3.2 Data collection and investigators

The data collection will be carried out by trained and blinded raters (doctors, physiotherapists) at baseline, post-intervention and at the follow-up call. After the end of the intervention, the participants' experience and acceptance of the intervention will be assessed in focus groups. A follow-up call will take place one month after the end of the intervention, i.e. two months after the baseline assessment. This survey will include a very short interview, the fall rate during the 4-week intervention period and two questionnaires (FOGQ, FES-I).

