| Depression                                                                                                                               | Beck Depression Inventory-II (BDI-II)                                                                                     |  | X |   | X |   |
| Fall rate                                                                                                                                | Number of falls (a) in the 3-month period before study entry (BL), (b) intervention period (PI) and (c) 4-week follow-up. |  | X |   | X | X |
| Feasibility of a larger randomised controlled trial                                                                                      |                                                                                                                           |  |   |   |   |   |
|                                                                                                                                          | Recruitment rate                                                                                                          |  | X |   |   |   |
|                                                                                                                                          | Retention rate                                                                                                            |  |   |   | X | X |
|                                                                                                                                          | Adherence rate                                                                                                            |  |   | X |   |   |
|                                                                                                                                          | Adverse events                                                                                                            |  |   | X | X |   |
|                                                                                                                                          | Acceptance of the intervention (continuous: narrative; focus groups in intervention group 1)                              |  |   | X | X |   |

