Differences between the two groups and test times are calculated for ordinal data as follows: New variables are generated from the difference between the post-intervention and baseline data. The difference between group 1 and 2 is determined using the Mann Whitney-U test. For the ordinal variables FES-I and FOGQ, which are also collected at the follow-up call, a Kruskal Wallis test is performed across all groups and test time points. Changes in fall rate (nominal) between baseline, post-intervention and follow-up will be calculated using Chi-Square test. Metric data will be tested for homogeneity of variance (Levene test) as the basic assumption of a 2 x 2 ANOVA, with "time (baseline, post-intervention)" as the within-factor and "group (1, 2)" as the between-factor. If there is no homogeneity of variance, an alternative F-statistic (e.g. according to Welch or Brown-Forsythe) is used. If the basic assumption of sphericity is not met, corrected values are used, e.g. according to Greenhouse-Geisser or Huynh-Feldt. To calculate the differences between the groups and measurement times, a 2 x 2 ANOVA (analysis of variance) is performed, followed by pairwise comparisons (Bonferroni correction for all comparisons) between the groups at measurement times 1 and 2 if statistical significance is present. In the case of failure of the adaptive measures, non-parametric tests are used as described for ordinal scaled data.

The effect size is given by partial Eta squared and standardised effect size (Cohen's d).

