# Instructor Manual for Physiotherapists

## General notes:

- Before the start of the programme, ask about the current health status of the participants.
- The exercises should be performed with the aim of achieving the greatest possible amplitude.
- Participants are allowed to take a break at any time.
- Use physiotherapy equipment as available e. g., chairs, stools, gym mats, gym balls, tennis balls, cones, ropes, step stools, dumbbells, balance boards, coordination hoops, rice, and beans bags.
- Add walking training with different variations (e.g., heel to toe, lateral walking, walking in reverse, crossing obstacles during walking, walking through a slalom course, changing walking directions and speed)
- Add stair climbing training
- The exercises to be carried out are constantly adapted to the participants individually, increasing movement speed as possible, in the course of the 4-week therapy within the given standardised framework.
- The documentation template starts on page 24. As the performing physiotherapist, please document here the exercises performed in the respective weeks with the increase (progression) performed (I-III) and the gaze fixation points performed (A-C).
- If participants feel insecure, they can always hold on to the wall or a chair. Assistance can be given if needed.

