Details of any falls

| Number of falls | Reason for the fall (e.g. dizziness, black ice, stumbling, etc.) |
|-----------------|------------------------------------------------------------------|
|-----------------|------------------------------------------------------------------|

During the training

Outside the training

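### Falls are observed and asked about during the intervention but only asked about before and after, and section 5.6.1 compares the three periods without allowing for this

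*Protocol*

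**What the plan says.** Section 4.4.13 defines three windows and how falls are found in each:

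- before the study: "a) in the 3-month period before the start of the study (subjectively asked at baseline"
- intervention: "b) in the 4-week intervention period (observed and subjectively asked about post-intervention"
- follow-up: "c) in the 4-week follow-up period (subjectively asked during the follow-up call"

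Table 2 in section 4.3.3 lists the same windows: "Number of falls (a) in the 3-month period before study entry (BL), (b) intervention period (PI) and (c) 4-week follow-up".

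The only inferential analysis that section 5.6.1 names for falls is across time: "Changes in fall rate (nominal) between baseline, post-intervention and follow-up will be calculated using Chi-Square test". The synopsis repeats it. Neither place names a test of falls between the arms, although the fall-rate hypotheses in 2.4 and 2.5 concern a difference between the two programmes.

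Two further places bear on the count.

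- Both instructor manuals contain study diaries for weeks 1 to 4 with a block headed "Details of any falls", split into falls during and outside training. The manuals address the therapist: "As the performing physiotherapist, please document here the exercises performed in the respective weeks". Section 4.4.13 does not mention these diaries.
- Section 4.3.2 describes the follow-up call as collecting "the fall rate during the 4-week intervention period and two questionnaires (FOGQ, FES-I". This names a different window from Table 2 and 4.4.13(c).

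**The concern.** A comparison across periods is interpretable only if a fall has about the same chance of being counted in each. Here the middle period adds observation to questioning and the outer two do not. The recorded count can therefore change between periods when the true rate has not: up from baseline to intervention, and down from intervention to follow-up. A real reduction from baseline could be hidden, and a drop after the intervention could be exaggerated.

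This is separate from the unequal window lengths and from the choice of test. The intervention and follow-up windows are both 4 weeks long, and the difference in capture would remain after conversion to falls per week and under any other test.

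**Working it through.** **1. The windows side by side**

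| Window | Length | Capture (4.4.13) | Assumed share of true falls found |
|---|---|---|---|
| (a) before study | 3 months | asked at baseline | 0.60-0.90 |
| (b) intervention | 4 weeks | observed and asked | 0.95-1.00 |
| (c) follow-up | 4 weeks | asked by telephone | 0.80-0.95 |

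The last column is assumed, because the protocol gives no recall sensitivity and no expected fall rate. The only design figure used is the sample size: 30 / (1 - 10/100) = 33.3, rounded up to 34, which reproduces section 4.1.2.3. It enters step 5 and an illustration in step 3.

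**2. Formula.** With an unchanged true rate, recorded rate = true rate x share found. In the ratio of two periods the true rate cancels, so the apparent ratio is the ratio of the shares.

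**3. As planned, no true change**

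- Follow-up/intervention: 0.80/1.00 = 0.80 to 0.95/0.95 = 1.00.
- Intervention/baseline: 0.95/0.90 = 1.06 to 1.00/0.60 = 1.67.

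In counts, assuming 0.5 true falls per person per 4 weeks: 34 x 0.5 = 17.0 falls at full capture in the intervention period, against 17.0 x 0.80 = 13.6 at follow-up at the low end.

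**4. Recalled counts only, same assumptions**

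- Follow-up/intervention: the same question over the same length of time, so the ratio is 1 if 4-week recall works equally well in both windows.
- Intervention/baseline: 0.80/0.90 = 0.89 to 0.95/0.60 = 1.58.

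Using recalled counts therefore repairs the first comparison but not the second. What remains in the second is the difference between 3-month and 4-week recall.

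**5. Effect on the test.** A simulation applied a Pearson chi-square to faller yes/no by period, which is one reading of the planned analysis. It used 34 people per period, 20,000 runs and a constant true rate of 0.25 to 1.0 falls per person per 4 weeks (assumed). Periods were treated as independent, as the planned test treats them. All windows were set to 4 weeks to isolate capture, and both recall-only periods were given the same share.

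| Recall finds, relative to intervention period | Rejections at the 5% level |
|---|---|
| 100% | 5.1-5.3% |
| 90% | 5.5-6.3% |
| 70% | 10-18% |
| 50% | 22-53% |

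Only the first two rows lie inside the 0.80-1.00 range of step 3. The lower two show what much poorer recall would do.

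**The case against.** The strongest reply is the randomised control arm. Section 4.4.13 draws no distinction between arms, and both manuals carry the same falls block. An artificial rise and drop would appear in both arms. A reader might infer that gaze training would look harmful during the programme and beneficial afterwards; the documents do not support that. This part of the reply stands. It does not dispose of the point, because 5.6.1 and the synopsis name only the across-period test for falls, so the protection offered by the control arm is not used in the stated analysis.

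Other parts of the reply also stand:

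- **The diary.** A reader might count three sources in the intervention period. The diary is therapist documentation, and the protocol does not say whether it feeds the endpoint; it may simply be where observed falls are written down. The point rests on observation plus questioning against questioning alone.
- **The larger trial.** A reader might infer that the future sample size would be distorted. Section 5.6.1 bases it on mean differences between groups, not on trends over time.
- **Size and direction.** Every sensitivity is assumed. Recall can also move older falls into a window, which works the other way. At 90% relative recall the test is barely affected.
- **Larger problems nearby.** In the same simulation, the 3-month baseline window alone, with perfect capture and no true change, gives 87-98% rejections. The intervention period is also a supervised inpatient stay, so the true rate may differ. Equal capture would not make the across-period comparison causal.

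The last item argues for a low grade, not for leaving the matter. Windows (b) and (c) have equal length, so window length cannot explain a difference between them, while unequal capture can. It is avoidable, and once the sources are merged into a single CRF number the recalled count may not be recoverable.

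**Conclusion.** The point holds in a limited form. The protocol fixes unequal capture in 4.4.13 and, in 5.6.1, a comparison that needs equal capture. With an unchanged true rate, the intervention count can exceed that of both other periods. Under the assumed sensitivities the follow-up/intervention ratio is 0.80-1.00, a range that includes no distortion at all; size and net direction cannot be settled from the documents. Comparisons of the arms within a period are not biased by this. Severity is minor: one secondary endpoint of a 34-person pilot whose inference the protocol itself calls preliminary.

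**What to change.** **Section 4.4.13.** For the intervention window, record two numbers: the patient's recalled count, obtained with the same question as at follow-up and before any record is consulted, and the all-source count. State whether the weekly diaries contribute to the all-source count.

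**Section 5.6.1 and the synopsis.**

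- Use recalled counts for follow-up versus intervention.
- Use the all-source count to compare the arms within the intervention period, which is the question 2.4 and 2.5 ask.
- Report any comparison with the 3-month baseline as descriptive only, because the 0.89-1.58 range remains even with recalled counts.

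**Section 4.3.2.** Reconcile the content of the follow-up call with Table 2 and 4.4.13(c), since the follow-up count depends on which window the call asks about.

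**Cost.** One extra CRF field and a few sentences. The across-period comparison then uses a less complete count. Questioning or recording during the intervention may still sharpen the patient's recall for that window, so the imbalance is reduced rather than certainly removed.
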